## **Study Design**

Consecutive individuals with PF from outpatient physical therapy clinics in 6 U.S. states will be screened for eligibility criteria and recruited. For patients to be eligible, they need to meet the following criteria: 1, a clinical diagnosis of PF in accordance with the clinical practice guidelines from the American Physical Therapy Association; 2, plantar heel pain for longer than 3 months; 3, first-step pain in the morning during the previous week rated at least 2 on NPRS; and 4, aged 18 years or older. Patients will be excluded if any of the following criteria are present: 1, a history of surgery to the ankle, foot or lower leg; 2, contraindications to manual therapy, dry needling, exercise or ultrasound; 3, have had physical therapy, acupuncture, massage therapy, chiropractic treatment or local steroid injections for PF in the previous 4 weeks; 4, present with 2 or more positive neurologic signs consistent with nerve root compression; 5, have another cause of heel pain (including tarsal tunnel syndrome, calcaneal fracture, ankle or foot instability, arthritis of the foot or ankle, rheumatoid arthritis, neurogenic claudication, peripheral neuropathy); or 6, have involvement in litigation or worker's compensation regarding their heel pain. Patients will also be excluded if they are pregnant. All participants will sign an informed consent prior to participation in the study.

Following baseline examination, patients will be randomly assigned to receive manual therapy, exercise and ultrasound alone or combined with electrical dry needling. Concealed allocation will be conducted using a computer-generated randomized table of numbers. Individual and sequentially numbered index cards with the random assignment will be prepared for each of the data collection sites. The index cards will be folded and placed in sealed opaque envelopes. Blinded to the baseline examination, the treating physical therapist will open the envelope and proceed with treatment according to the group assignment.

All participants in both groups will receive up to eight treatment sessions at a frequency of once

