
In addition to the 8-point standardized protocol, therapists will also be permitted to insert needles at up to 4 additional locations in the foot and/or lower leg based on the presence of trigger points, or the report of sensitivity by the patient. The medial head of the gastrocnemius is recommended as one of the four optional needle insertion sites. Following insertion, needles will be manipulated bi-directionally to elicit a sensation of aching, tingling, deep pressure, heaviness or warmth, and then left in situ for 20 mins with electric stimulation (ES-160 electrostimulator ITO co.) using a low frequency (2 Hz), moderate pulse duration (250 microseconds), biphasic continuous waveform at an intensity described by the patient as “mild to moderate”.

The primary outcome will be first-step pain during the morning as measured by the Numeric Pain Rating Scale (NPRS). Secondary outcomes will include resting mean foot pain (NPRS), pain during activity (NPRS), the Lower Extremity Functional Scale (LEFS), the Foot Functional Index (FFI), medication intake, and the Global Rating of Change (GROC) at baseline, 1 week, 4 weeks and 3 months. Medication intake will be measured as the number of times the patient has taken prescription or over-the-counter analgesic or anti-inflammatory medication in the past week for their heel pain, with five options: (1) not at all, (2) once a week, (3) once every couple of days, (4) once or twice a day, or (5) three or more times a day. Medication intake will be assessed at baseline and at 3 months. In addition, the Global Rating of Change (GROC) will be collected at 1 week, 4 weeks and 3 months following the initial treatment session.

In order to detect treatment differences of 2 points on the main outcome (i.e. the MCID for NPRS on first-step pain), and assuming a standard deviation of 3 points, a 2-tailed test, an alpha level of 0.05 and a desired power of 90%, the estimated desired sample size is calculated to be at least 49 subjects per group. A dropout percentage of 10% is expected, so 53 patients will be included in each group.

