Statistical analyses will be performed using SPSS and conducted according to intention-to-treat analysis for patients in the group to which they are first allocated. Mean, standard deviations and/or 95% confidence intervals will be calculated for each variable. Baseline demographic and clinical variables will be compared between both groups using independent Student t-tests for continuous data and  $\chi^2$  tests of independence for categorical data. The effects of treatment on first-step pain intensity, resting foot pain, pain during activity, physical function, and related-disability will each be examined with a 2-by-4 mixed model analyses of covariance (ANCOVA) with treatment group (conventional physical therapy vs. conventional physical plus electrical dry needling) as the between-subjects factor, time (baseline, 1 week, 4 weeks and 3 months follow-up) as the within-subjects factor, and adjusted for baseline data for evaluating between-groups differences. Separate ANCOVAs will be performed for first-step pain intensity, mean heel pain at rest, pain during activity, the Lower Extremity Functional Scale, the FFI Total Score, the FFI Pain Subscale, the FFI Disability Subscale, and the FFI Activity Limitation Subscale as the dependent variable. For each ANCOVA, the main hypothesis of interest will be the 2-way interaction (group by time) with a Bonferroni-corrected alpha of 0.0125 (4 time points). We will use  $\chi^2$  tests to compare self-perceived improvement with GROC and changes in medication intake. To enable comparison of between-group effect sizes, standardized mean score differences (SMDs) will be calculated by dividing mean score differences between groups by the pooled standard deviation. Numbers needed to treat and 95% confidence intervals will also be calculated at the 3-months follow-up period using each definition for a successful outcome.

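### The Bonferroni alpha of 0.0125 for four time points matches no set of four tests in the plan, and it conflicts with the 0.05 used to size the trial

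*Protocol*

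**What the plan says.** All of this is in the Study Design section of the protocol.

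- **Test and threshold** (statistical analysis paragraph): "For each ANCOVA, the main hypothesis of interest will be the 2-way interaction (group by time"), to be judged "with a Bonferroni-corrected alpha of 0.0125 (4 time points").
- **Time factor and covariate** (same paragraph): the model has "time (baseline, 1 week, 4 weeks and 3 months follow-up) as the within-subjects factor", and it is also "adjusted for baseline data for evaluating between-groups differences".
- **Order of events** (randomisation paragraph): "Following baseline examination, patients will be randomly assigned".
- **Primary outcome** (outcomes paragraph): a single one. "The primary outcome will be first-step pain during the morning as measured by the Numeric Pain Rating Scale (NPRS").
- **Sample size** (sample size paragraph): "In order to detect treatment differences of 2 points on the main outcome", with an SD of 3, "a 2-tailed test, an alpha level of 0.05 and a desired power of 90" per cent. This leads to at least 49 per group, raised to 53 for dropout.

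**The concern.** A Bonferroni divisor should equal the number of tests that share the error rate. The protocol divides by the number of measurement occasions, yet applies the result to an interaction that already spans those occasions in one test. One of the four occasions is baseline. It is measured before allocation and is also a covariate, so it cannot supply a treatment comparison.

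The stake is the primary conclusion. A first-step-pain result with p between 0.0125 and 0.05 would be reported as negative because of a correction with no matching tests, in a trial whose stated 90% power was calculated at 0.05. Relaxing the threshold once data are seen would be hard to defend, so it needs settling beforehand.

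**Working it through.** **1. Reproduce the threshold.** 0.05/4 = 0.0125. The arithmetic is right; the question is the 4.

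**2. Count the tests.**
- Interaction in a 2-by-4 design: (2 − 1) × (4 − 1) = 3 numerator degrees of freedom, one F statistic, one p-value. Divisor 1, alpha 0.05.
- Group comparisons by visit: 4 − 1 = 3 occasions after randomisation. Divisor 3, alpha 0.05/3 = 0.0167. Three tests at 0.0125 use 3 × 0.0125 = 0.0375 of the available 0.05.

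**3. Reproduce the sample size.** Inputs from the protocol: difference 2, SD 3, two-sided 0.05, power 90%. For a two-sample t-test with n = 49 per group, the degrees of freedom are 2 × 49 − 2 = 96 and the noncentrality is 2 / (3 × √(2/49)) = 3.30. Power is 90.4%; with 48 it is 89.8%. So 49 is the smallest adequate n at alpha 0.05.

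**4. Same model, other thresholds.**

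| Two-sided alpha | Power, 49 per group | Power, 53 per group (nobody lost) | n per group for 90% |
|---|---|---|---|
| 0.05 | 90.4% | 92.5% | 49 |
| 0.0167 | 80.4% | 83.9% | 63 |
| 0.0125 | 77.3% | 81.1% | 66 |

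The shortfall at 0.0125 is 90.4 − 77.3 = 13.1 points against 0.05, and 80.4 − 77.3 = 3.1 points against 0.0167.

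**5. Allow for baseline adjustment.** The protocol gives no baseline-to-follow-up correlation r, so a range is assumed. Residual SD = 3 × √(1 − r²), n = 49, difference 2:

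| Assumed r | Residual SD | Power at 0.05 | Power at 0.0125 | Loss (points) |
|---|---|---|---|---|
| 0.3 | 2.86 | 92.8% | 81.7% | about 11 |
| 0.5 | 2.60 | 96.5% | 89.4% | about 7 |
| 0.7 | 2.14 | 99.6% | 98.0% | about 2 |

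**6. The interaction itself.** Steps 3 to 5 concern one visit. For the four-level interaction, assume equal correlation ρ between all occasions, SD 3, n = 49 and no covariate. The noncentrality is (n/2) × Σ(dₜ − mean d)² / (9 × (1 − ρ)), where dₜ is the group difference at occasion t, on 3 and 3 × 96 = 288 degrees of freedom. With differences 0, 2, 2, 2 the sum of squares is 1.5² + 3 × 0.5² = 3.

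| Assumed ρ | Differences 0, 2, 2, 2: power at 0.05 / 0.0125 | Differences 0, 0.67, 1.33, 2: power at 0.05 / 0.0125 |
|---|---|---|
| 0.3 | 82.3% / 65.2% | 68.4% / 47.7% |
| 0.5 | 93.6% / 83.8% | 83.7% / 67.3% |
| 0.7 | 99.6% / 98.3% | 97.4% / 92.1% |

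The loss runs from about 1 to about 21 points, depending on a correlation and an effect shape that the protocol does not state.

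**The case against.** The strongest defence is that the rule errs on the safe side. Anything significant at 0.0125 is also significant at 0.0167 and 0.05, so no false-positive claim is at risk. That stands, and it limits the point to power and internal consistency.

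The defence is also right that the 13-point loss is the least favourable simple comparison. It uses the divisor-1 reading and an unadjusted test at one visit. On the divisor-3 reading the threshold is 0.0167/0.0125 = 1.33 times stricter, not four times, and the loss is about 3 points. With baseline adjustment at r = 0.5, power at 0.0125 is 89.4%, close to the planned 90%. A reader might take 13 points as the established cost to this trial; the documents do not support that, because the analysis differs from the sizing model and the correlations are not given.

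Two further inferences should be resisted. One is that a single threshold for eight ANCOVAs leaves outcomes uncorrected. The protocol names one primary outcome and does not say that the secondary ones carry confirmatory claims, so that is a separate matter. The other is that 3 months is the primary contrast. The protocol names no primary time point and singles out 3 months only for numbers needed to treat and for medication intake.

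The order of any visit-wise contrasts may properly be left to a statistical analysis plan. That does not rescue the 0.0125, which the protocol itself fixes and explains by the four time points.

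**Conclusion.** The point holds in limited form. A divisor of four corresponds to no family of tests that the protocol names: it is one for the interaction and three for visit-wise comparisons. The decision threshold also disagrees with the sample size paragraph. On the protocol's own sizing model, the stated 90% power becomes 77.3% at the threshold actually specified.

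That figure rests on 49 evaluable patients per group, difference 2, SD 3 and an unadjusted comparison at one visit. Under baseline adjustment the loss against 0.05 is about 2 to 11 points for assumed r of 0.7 to 0.3. For the interaction the size cannot be fixed from the document, though its direction is certain, since a smaller alpha always lowers power. Type I error is not inflated, and a positive result under the present rule would remain sound.

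**What to change.** Delete the 0.0125 and its four-time-points reason, then state one of the following.

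- **Single test:** test the interaction for first-step pain, the primary outcome, at two-sided 0.05, matching the alpha in the sample size.
- **Visit-wise tests:** if contrasts at each visit are the intended confirmatory tests, use 0.05/3 = 0.0167 for each of the three post-baseline visits, or a fixed order chosen by the sponsor with each at 0.05.

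Restate the power at the alpha adopted. At 0.0167, the protocol's own model gives 80.4% with 49 per group.

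Keep baseline as the covariate only, not also as a level of time. This needs care under the single-test option. With only three follow-ups as levels, the interaction has 2 degrees of freedom and asks whether the group difference changes between follow-ups. A constant benefit of 2, 2, 2 has deviations of zero, so that test alone could not detect it. The single test should therefore be worded as the joint test of the group terms (group plus group-by-time, 1 + 2 = 3 degrees of freedom).

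The cost is a few sentences in the analysis and sample size paragraphs, made before outcome data are seen. No extra data are needed. Recruitment changes only if the sponsor chooses the stricter alpha and still wants 90% power on the sizing model (63 evaluable per group at 0.0167).

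### The chi-square tests planned for medication change and GROC ignore category order, and medication has no baseline covariate: a cheap gain in power is missed on two secondary outcomes

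*Protocol*

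**What the plan says.** All of this is in the protocol, Study Design.

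- **Scale.** Medication intake is how often analgesic or anti-inflammatory medication was taken for heel pain in the past week, "with five options: (1) not at all, (2) once a week, (3) once every couple of days", and so on up to three or more times daily. The options are ordered.
- **Timing.** The list of secondary outcomes ends with "medication intake, and the Global Rating of Change (GROC) at baseline, 1 week, 4 weeks and 3 months". More specific sentences then narrow this: "Medication intake will be assessed at baseline and at 3 months", and "the Global Rating of Change (GROC) will be collected at 1 week, 4 weeks and 3 months following the initial treatment session". I follow the specific sentences.
- **Test.** The statistical paragraph assigns chi-square "tests to compare self-perceived improvement with GROC and changes in medication intake". It names no table layout, trend version, stratification or covariate for these two outcomes.
- **Contrast.** The pain, function and disability scores go into models "adjusted for baseline data for evaluating between-groups differences".
- **Success definitions.** Numbers needed to treat are to be "calculated at the 3-months follow-up period using each definition for a successful outcome". The definitions themselves are not given.

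**The concern.** A Pearson chi-square gives the same result however the columns of the table are permuted. It spreads its sensitivity over every possible pattern of difference, whereas the pattern of interest is a consistent shift towards less medication or more improvement. With about 48 patients per arm, such a shift can be missed. When there are more than two categories, a significant result also does not show that one arm did better.

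For medication, the baseline value is available but is used only through the change. A change between two five-point categories can take nine values (−4 to +4), many of them sparse, or it can be collapsed in several ways. A baseline covariate would use the same information more efficiently and leave less to choose.

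**Working it through.** **1. The plan's own figure.** For first-step pain: difference 2, SD 3, two-sided alpha 0.05, power 90%. The normal approximation gives n = 2 × (1.960 + 1.282)² × 3² / 2² = 47.3, so 48 per group. The t-based calculation gives 49 (power 90.4%), which matches the protocol. No power is stated for GROC or medication. With 53 enrolled per group and 10% dropout, 53 × 0.9 = 47.7, so I take 48 analysed per arm.

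**2. A check that needs no category rates.** A 1-df ordered test with 80% power has noncentrality (1.960 + 0.842)² = 7.85. A 4-df chi-square with the same noncentrality has 60% power. For 90% power the noncentrality is 10.51, and the 4-df test has 74%. This supposes that the whole effect lies along the ordering.

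**3. Medication at 3 months, simulated.** Assumptions, none of them from the protocol:
- control distribution at 3 months 30/20/20/20/10%, baseline distribution 20/15/25/25/15%;
- a common odds ratio (OR) for treatment;
- latent baseline correlation 0.3, 0.5 or 0.7;
- alpha 0.05 and 2,500 runs per scenario, so the Monte Carlo standard error is at most √(0.25/2500) = 1 point.

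To give the ORs a scale: with 30% of controls taking none, the odds are 0.30/0.70 = 0.429. OR 2 then gives 0.857/1.857 = 46% taking none, and OR 3 gives 1.286/2.286 = 56%.

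| OR | Chi-square, 5 levels | Rank test | Gap (points) | 2×2: none v any | Ordered score model with baseline |
|---|---|---|---|---|---|
| 2 | 27–29% | 47–48% | 18.3–20.7 | 37–38% | 49–67% |
| 2.5 | 45–47% | 68–69% | 21.1–23.5 | 58–60% | 71–86% |
| 3 | 60–62% | 82–84% | 20.5–22.1 | 75–76% | 84–95% |

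Ranges run over the three correlations. For the unadjusted 3-month tests the correlation is irrelevant, so that spread is simulation error. The last column is a linear model on the category score, standing in for the proportional-odds model.

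With three assumed control distributions, chi-square against rank test was 24–28% v 42–46% at OR 2 and 51–66% v 76–86% at OR 3; a dichotomised table had 57–79% at OR 3. Over all of this, the five-level loss at OR 2 to 3 is about 17 to 25 points.

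**4. Medication as a change.** At OR 3, for correlations 0.3 / 0.5 / 0.7:
- chi-square on the nine-level change: 26% / 37% / 57%;
- rank test on the change: 62% / 71% / 86%;
- chi-square on improved v not improved: 40% / 51% / 65%.

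The 2×2 table thus loses about 20 to 21 points against the rank test on the change, and the nine-level table about 29 to 36. In each setting the 2×2 loses less than the full table it replaces, but the amount depends on the cut: 7 to 9 points for none v any at 3 months at OR 3, about 20 for improved or not.

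**5. GROC.** Assumed: 15 levels from −7 to +7, success at +5 or above, 37% success in controls. At OR 3 the rank test has 85%, the 2×2 success table 77% (loss 85 − 77 = 8 points), and the 15-level chi-square 40% (loss 45 points).

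**6. Type I error.** With no effect, the chi-square tests rejected in about 3 to 5% of runs. The lowest values were for the sparse nine-level and 15-level tables. There is no inflation.

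**The case against.** The strongest reply is that the table layout is not stated. The sentence on GROC speaks of improvement, and the paragraph later refers to definitions of success, so a 2×2 comparison is a natural reading. On that reading the chi-square suits the measure, a significant result does have a direction, and the loss is modest. That stands, and it limits the GROC part of this point.

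A reader might infer that the plan discards baseline medication. It does not: the comparison is of changes, so baseline enters there. What remains is that it is neither covariate nor stratum. GROC is itself a rating of change and has no baseline to adjust for.

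A reader might also take the 40% v 85% contrast for GROC as the expected loss. The protocol gives neither the length of the GROC scale nor a plan to tabulate every level, so that is a worst case.

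The simulations use a common odds ratio, the alternative that favours rank and proportional-odds methods; no non-proportional effect was tried. This also stands. For an effect that moved patients towards both ends of the scale, the chi-square could do better.

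Finally, the coding of change and the grouping of GROC may properly sit in a statistical analysis plan that is not at hand, and their absence is not held against the protocol. But the protocol does choose the test, and with it forgoes order on every layout.

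**Conclusion.** The point holds as a missed improvement, not as an error that threatens the trial. For medication, an unordered five-level chi-square costs about 17 to 25 points of power against a rank test at OR 2 to 3, and more against an ordered analysis with baseline as covariate. Dichotomising reduces the loss relative to the corresponding full table but does not remove it. For GROC the cost is about 8 points at OR 3 as a 2×2 success measure, and large only with all levels tabulated.

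These sizes rest on assumed category distributions, 48 analysed per arm, alpha 0.05 and a proportional-odds effect. The direction of the loss is secure for a consistent shift; its exact size is not. It would be wrong to conclude that the tests are invalid or that the main result is at risk: type I error is kept, both outcomes are secondary, no power is claimed for them, and the analysis of first-step pain is untouched.

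**What to change.** - **Medication.** Analyse the 3-month category by proportional-odds regression on treatment and baseline category. Report the common odds ratio with its 95% confidence interval.
- **GROC.** Use a rank or proportional-odds test at the follow-up visits, with 3 months named as the key visit.
- **Binary success.** Keep the chi-square test or a risk difference only for a success definition fixed in advance, and state that definition.

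The cost is a few sentences of wording. No further data or patients are needed, and SPSS, which the protocol already names, fits the model. The downside is the proportional-odds assumption, which should be checked and reported. If it fits poorly, the odds ratio is best read as an average over the cut-points, beside the category percentages by arm.
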